In order to measure the impact of the first episode of ARI or SARI on functional status, we will conduct a nested case-control study of participants recovering from an ARI or SARI. Participants who experience their first ARI or SARI after enrollment will be matched with cohort participants who have not yet experienced an ARI or SARI based on age ( $\pm 5$  years), sex, influenza vaccination and most recent functional status measurement. Interviews will be conducted three to four weeks after the onset of ARI or SARI in the case and both cases and controls will be compared with respect to changes in functional status measurement (VES-13 score  $\geq 3$ ).

Elderly with COPD: In the standardized baseline questionnaire assessing functional status and medical conditions, participants will be asked whether they have been diagnosed with COPD. If they do, at the end of two years, the number of outpatient visits and inpatient admissions for exacerbations of COPD will be determined (by directly observing their medical records). A COPD exacerbation is defined as “a sustained worsening of the patient's condition, from the stable state and beyond normal day-to-day variations that is acute in onset and may warrant additional treatment in a patient with underlying COPD” (11). We will use the collected nasal self-swabs or healthcare worker collected nasopharyngeal swab taken when the participant was experiencing an ARI or SARI to confirm whether the COPD exacerbations the participant experienced were influenza-associated. At the end of the study, the incidence of all-cause COPD exacerbations and laboratory confirmed influenza-associated COPD exacerbations among the elderly with COPD who fit the ARI or SARI case definitions will be calculated. The incidence among those who were vaccinated will be compared to those who were not vaccinated.

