Pilot studies: Vaccination coverage of persons aged 65 years and older in Nakhon Phanom is low, and targeted towards the elderly who also have underlying chronic conditions. The Provincial Medical Office undertook a pilot study in four districts from June-November 2014 to evaluate strategies to increase the vaccination rate and identify factors, such as functional status and chronic medical conditions that are significantly associated with vaccination. The information gained from this study will allow increased precision in sample size estimates and improved measurement of potential confounders. Another pilot study was conducted from February to March 2015 that studied the acceptability, accuracy and validity of taking nasal self-swabs. Of the total 108 participants in the study, all 108 participants (100%) felt that taking the nasal swab by themselves was acceptable, Sixteen participants (15%) felt uncomfortable taking the swab by themselves; however, 107 participants (99%) felt that nasal self-swabbing was easy to perform. Out of the 109 nasal self-swab samples collected, 106 (97.2%) were able to detect RNaseP<37, an indicator that the samples were taken accurately. We are still in the process of analyzing the validity of the data collected.

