Elderly with certain underlying medical conditions, such as chronic obstructive pulmonary disease (COPD), are especially at high risk from influenza. COPD is a respiratory illness characterized by irreversible airflow obstruction. In 2010, COPD was the sixth leading cause of death in Thailand (23), and in 2002, the prevalence of COPD among the elderly around Bangkok was 7.11 percent(24). Influenza exacerbates COPD symptoms, and vaccinating individuals with COPD can reduce the risk of hospitalizations, morbidity and mortality (25). One study from the United Kingdom showed that influenza vaccination reduced the risk of all-cause mortality in COPD patients by 41% between December and March(26). Another study conducted in the United states among elderly persons with COPD found that the risk of hospitalization due to pneumonia or influenza was reduced by 48% from influenza vaccination (27). A study conducted in the United States among elderly persons during the influenza season found hospitalization costs due to acute and chronic respiratory conditions to be 42% lower in those that were vaccinated (28). A cost effectiveness analysis in Thailand found that depending on the severity of COPD, for every 100 persons with COPD that receive the influenza vaccine, roughly 125,629 to 680,647 Thai Baht was saved (29, 30). To date, there is only one study that examined vaccine efficacy among persons with COPD who were mostly elderly in Thailand. This randomized controlled trial of the efficacy of IIV3 among persons with COPD in Bangkok, Thailand, to prevent influenza-associated ARI found a vaccine effectiveness (VE) of 76% (30). Because the Thailand MOPH is prioritizing adults with COPD to be vaccinated with influenza, and the

elderly with COPD are at heightened risk, more research is needed to confirm the vaccine effectiveness of trivalent IIV3 influenza vaccine among the elderly with COPD in Thailand to support future protocols.

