## **5. Objectives**

### **1. Primary Objectives**

1.1: Measure the incidence of laboratory-confirmed influenza-associated ARI and SARI among a cohort of persons aged 65 years and older in 2 districts in Nakhon Phanom Province and calculate vaccine effectiveness by comparing incidence between persons who did and did not receive IIV3, controlling for potential confounders.

1.2: Assess the medical costs (direct and indirect) associated with influenza infections among the elderly and estimate the savings from vaccination based on varying levels of vaccine coverage, and evaluate the value for money of the influenza vaccine campaign program for persons aged 65 years and older

1.3: Among persons aged 65 years and older with COPD, measure the incidence of influenza-associated COPD exacerbations meeting ARI or SARI case definitions, and all-cause exacerbations and compare incidences between vaccinated and unvaccinated persons

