To estimate the incidence of influenza-associated COPD exacerbations among elderly with COPD, we will calculate the total number of laboratory-confirmed influenza-associated COPD exacerbations per total number of COPD patients within our cohort over a year (primary objective 1.3). We will compare the incidence among those that were vaccinated with IIV3 versus those that were not vaccinated with IIV3. In order to account for correlation among repetitive measurements from each individual, we will also employ GEE methodology. This method will also allow us to adjust for underlying confounders such as smoking history and age.

Blood samples will be taken from a select number of participants who will have had IIV3 to test the antibody response of IIV3 among the elderly (objective 2.2). These blood samples will be taken at baseline before receiving the shot, and then again after 28 days (1 month), 180 days (6 months), and 360 days (12 months) later. The blood samples will be tested for HI antibodies. Everyone with a baseline HI assay  $\geq 10$  who has a four-fold increase in HI antibody count post vaccination or who has a baseline HI assay  $< 10$  who has a post vaccination count  $\geq 40$  will be considered seroconverted against influenza. One additional blood draw will be taken after 28 days of subsequent vaccination in the second year to compare the effect of prior vaccination on level of immunological response. We will use a random effects model (RE) to compare blood

samples at the post vaccination dates to the baseline HI assay to determine how long participants vaccinated with IIV3 retain an adequate number of HI antibodies. RE allows us to control for the differences in antibody count amongst all individuals across unequal intervals and obtain a mean distribution. This methodology will also allow us to control for confounders such as age and factors which make participants immuno-compromised.

We will also evaluate a simpler outcome, the incidence rate of RSV among elderly with ARI or SARI over the entire observation period (second-objective 2.3), which should be similar between those that were vaccinated with Influenza IIV3 and those that were not.

Aggregate results may be shared with relevant CDC programs in which the findings of this study may have immediate policy implications. Opportunities for publication will be sought.

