## **Limitations**

The main limitation of this study is its limited generalizability to Thailand. While we are able to obtain a representative sample of Nakhon Phanom Province, the people in NP may be different than people from other parts of Thailand. Another limitation is sampling bias. The study's sample may be biased since healthier people are usually more willing to participate in studies compared to people who are more ill, which would not represent the target population of all types of elderly people. In order to diminish the potential of sampling bias, our inclusion criterion includes all elderly despite illness type.

It is possible that not all respiratory events in the enrolled elderly will be captured, due to inability to communicate, misunderstanding and even memory loss. To a large extent, a lot of the success for this project may rely on the relationship between the household and health volunteer and role of the caregiver for participants greater than 80 years of age. Another limitation to our study is that baseline enrollment data and weekly follow-up data is relying heavily on self-report. It is possible for participants to be unaware of whether they have certain underlying co-

morbidities if they do not regularly visit the physician, it is possible for them to under or overestimate their functional status, and it is possible for them to forget to take a nasal self-swab or remember that they even experienced an ARI or SARI. In order to mitigate these potential issues, we are using a reliable and sensitive functional status questionnaire and following-up with participants weekly in case they forget to call us.

Although Thailand provides free vaccinations for elderly, there are not enough purchased to vaccinate all elderly in Thailand. Due to the limited number of vaccines, elderly that are sicker and see health care professionals more often are more likely to become vaccinated than those who are healthier. The elderly who join our immunogenicity study will most likely be sicker than the general population and are more likely to be immunocompromised. Because of this selection bias, our immunogenicity study will most likely show a lower rate of seroprotection among the elderly than what is actually representative of the average elderly population.

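### Primary objective 1.3 compares COPD exacerbations by vaccination status without capturing prior exacerbations, COPD severity or maintenance treatment, so residual confounding is likely and the all-cause comparison is the most exposed

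*Protocol*

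**What the plan says.** Objective 1.3 (Protocol section 5) is a primary objective. Among people with COPD it will measure influenza-associated exacerbations and "all-cause exacerbations and compare incidences between vaccinated and unvaccinated persons".

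- **Outcome.** Section 3.1.4 says that, once follow-up is over, "the number of outpatient visits and inpatient admissions for exacerbations of COPD will be determined (by directly observing their medical records". Section 7.5.1 has a research nurse enter the dates and number of exacerbation visits on an electronic form.
- **Baseline COPD data.** Under section 3.1.4, "participants will be asked whether they have been diagnosed with COPD". Form 4b, items 33–34, asks for a physician diagnosis of chronic lung disease and its type.
- **Adjustment.** Section 7.9 applies generalised estimating equations (GEE) and adds: "This method will also allow us to adjust for underlying confounders such as smoking history and age". For the main VE model the same section also names co-morbidities, distance to a health facility and propensity score matching.
- **Who is vaccinated.** Section 3.1.4 describes vaccination in the province as "targeted towards the elderly who also have underlying chronic conditions". The Limitations section says: "Due to the limited number of vaccines, elderly that are sicker and see health care professionals more often are more likely to become vaccinated". It draws the consequence only for the immunogenicity study, not for objective 1.3.

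**The concern.** In an analysis restricted to people with COPD, the diagnosis no longer separates anyone. What separates them is how bad the disease is and how readily they seek care. On the protocol's own account both can influence vaccination, and both influence how many exacerbations reach a clinic record. The variable closest to this shared cause is the person's exacerbation count before enrolment, and the protocol does not say that it will be collected.

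A model or propensity score can use only collected variables, so a later analysis plan cannot supply this one by itself. At stake is whether a primary comparison shows the effect of the vaccine or a pre-existing difference between the groups. The all-cause endpoint matters most. Most exacerbations may not be due to influenza, so the true effect on it is small and a small imbalance can swamp it.

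**Working it through.** **1. The plan's own figures.** No sample size or expected effect is stated for objective 1.3. The only VE sample size is 2,724 (section 7.1.5). With 6% against 3.6%, two-sided 5%, 80% power, 1:1 and the Fleiss method with continuity correction, I get 1,327 per group, or 2,654. That is 2.6% below the stated figure, close enough to accept. The point does not rest on it.

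**2. Size of the COPD subset.** Enrolment is 3,133 (section 7.1.5). The COPD prevalence cited in section 4.2 is 7.11%, from Bangkok; that it applies here is an assumption. 0.0711 × 3,133 = 223, or about 111 per group at 50% vaccination.

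**3. What the forms hold.**

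| Item | Where |
|---|---|
| Severe illness and any-cause hospitalisation, last year | Form 4b, items 5–6 |
| Physical function, including walking half a kilometre and heavy housework | Form 4b, items 10–15 |
| Smoking amount and dates | Form 4b, items 49–53 |
| Usual place of care | Form 4b, item 57 |
| Lung function or COPD stage | No form shown |
| Exacerbations before enrolment | No form shown |
| COPD maintenance treatment | No form shown |

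Form 4h, item 11, mentions steroids as an example of immunocompromise. It goes only to immunogenicity participants, all of whom came for vaccination.

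**4. Bias formula.** Let c be the baseline exacerbation rate in vaccinated people divided by that in unvaccinated people, after whatever adjustment is made. Then observed rate ratio = true rate ratio × c, and c = 1 / true rate ratio erases the effect.

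**5. Influenza-confirmed exacerbations.** The true VE is either 40% (whole-cohort assumption, section 7.1.5) or 76% (the randomised COPD trial cited in section 4.2, against influenza-associated acute respiratory infection). The values of c are assumed. Apparent VE = 1 − 0.60c or 1 − 0.24c.

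| c | True VE 40% appears as | True VE 76% appears as |
|---|---|---|
| 1.25 | 25% | 70% |
| 1.5 | 10% | 64% |
| 2.0 | −20% | 52% |

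Erasing the effect needs c = 1/0.60 = 1.67 or c = 1/0.24 = 4.17.

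**6. All-cause exacerbations.** Let f be the share of exacerbations due to influenza (assumed 5–30%). True all-cause rate ratio = 1 − f × VE.

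| f | Rate ratio, VE 40% | c that erases it | Rate ratio, VE 76% | c that erases it |
|---|---|---|---|---|
| 5% | 0.98 | 1.02 | 0.96 | 1.04 |
| 10% | 0.96 | 1.04 | 0.92 | 1.08 |
| 20% | 0.92 | 1.09 | 0.85 | 1.18 |
| 30% | 0.88 | 1.14 | 0.77 | 1.30 |

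**7. What imbalance gives such a c.** For one unmeasured binary factor (severe or not), c = [1 + p_v(R − 1)] / [1 + p_u(R − 1)]. Here p_v and p_u are the severe shares in vaccinated and unvaccinated people, and R is the rate ratio of severe to other COPD. All three are assumed.

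- 40% against 30%, R = 3: 1.8/1.6 = 1.12, enough to reverse a true all-cause rate ratio of 0.96.
- 50% against 30%, R = 3: 2.0/1.6 = 1.25.
- 60% against 20%, R = 4: 2.8/1.6 = 1.75, needed before a true 0.60 becomes 1.05.

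**8. The opposite direction.** With severe shares of 30% in vaccinated and 50% in unvaccinated people and R = 3, c = 1.6/2.0 = 0.80. A true 0.60 then appears as 0.48, and a true all-cause 0.96 appears as 0.77, a spurious benefit.

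**9. Events available.** If the section 7.1.5 rates held in this subset, influenza-confirmed events would number 111 × 0.06 + 111 × 0.036 = 6.7 + 4.0, about 11 a year.

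**The case against.** Several points on the other side carry weight.

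- **The covariate list is open.** Smoking and age follow the words "such as", and a propensity model for vaccination is planned (section 3.1.1). A fuller list may sit in an analysis plan that is not at hand. This stands, so the wording of section 7.9 is not itself the fault. But an open list cannot include a variable that no one records.
- **Form 4b has relevant proxies.** Exertional limitation, smoking amount and last-year hospitalisation bear on COPD severity and will remove some confounding. None measures earlier exacerbations.
- **The COPD record form is not among appendix forms 4a–4i.** Its fields are known only from sections 3.1.4 and 7.5.1, which describe follow-up counts and no look-back. The gap can be stated only for what is shown and described.
- **The direction is not established.** A reader might infer that vaccinated patients will show more exacerbations and that a real benefit will be hidden or reversed. The documents do not support that. Targeting of chronic disease, and the statement in section 4.2 "Because the Thailand MOPH is prioritizing adults with COPD to be vaccinated with influenza", concern COPD against no COPD, not severe against mild COPD. The Limitations sentence concerns the elderly in general. Section 4.2 also cites poor function going with less vaccination. Section 7.5.1 requires all people with COPD to report to the COPD clinic for exacerbations, which may even out how events are captured.
- **The data are not lost.** A reader might also infer that nothing can be done later. The charts are still to be opened, so a look-back is possible until the identifying data are deleted after cleaning (section 7.7).

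**Conclusion.** The concern holds as a probable source of residual confounding in a primary comparison, with uncertain direction. It is not a demonstration that the result will be reversed.

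The two endpoints differ. The all-cause comparison is fragile: at VE 40%, an imbalance of 1.02–1.14 removes the whole true effect, and at VE 76% an imbalance of 1.04–1.30 does so. The influenza-confirmed comparison is sturdier. A true VE of 40% is noticeably attenuated at 1.25–1.5 and reversed only above 1.67. A true VE of 76% is attenuated but not reversed at any imbalance considered.

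These sizes rest on assumed imbalances, an assumed influenza share of 5–30%, and one or other of the two VE figures in the protocol. Uncertainty about direction is a reason to measure the baseline difference, since without it nobody can say which way the estimate leans.

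**What to change.** In the COPD record review already planned, also extract for the 12 months before enrolment the number of exacerbation visits and admissions, and any recorded maintenance treatment. Do this before the identifying data are deleted. Then:

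- Adjust the objective 1.3 GEE, chiefly the all-cause model, for the pre-enrolment exacerbation count. The count comes through the same records as the outcome, so it reflects both disease and care-seeking.
- In the influenza-confirmed model, where events will be few, keep added covariates to a minimum or carry them in the propensity score.
- Report the pre-enrolment exacerbation rate ratio by vaccination status as a balance check.
- State in the Limitations that selection into vaccination also affects objective 1.3 and that its direction is not known.

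The cost is a few extra fields and modest nurse time on roughly 220 charts, if the cited prevalence applies. Some records will be incomplete, and the number with a usable look-back should be reported by vaccination status.

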Laboratory testing of blood samples: In order to measure hemagglutination inhibition assay (HAI) antibody titers to check for duration of seroconversion in elderly from IIV3, blood samples will be requested from elderly arriving to the district hospitals vaccination clinics in That Phanom and Plapak for vaccination. The first sample will be taken just before vaccine is administered on day 0 (as a baseline measurement) and on day 28 (after 1 month), day 180 (after 6 months) and day 360 (after 1 year). One additional blood draw will be requested after 28 days of vaccination in the second year to compare the effect of prior vaccination on level of immunological response. Participants will be expected to go to their district hospital to have their scheduled blood draw. Blood will be drawn at the participant's home if they are unable to travel to their district hospital by a research nurse. Blood samples will be collected and immediately sent to the district hospital lab to separate the serum from the blood (if blood is collected at a participant's home, it can be transported back to the district hospital with the nurse at room temperature). The serum will be stored in a refrigerator between 4-8°C for no longer than seven days and transported to NIH on a weekly basis. During transport to NIH, serum samples will be stored with ice packs for less than 24 hours. Upon reaching NIH, the samples will be measured using a standard HAI (5). Seroconversion will be measured as the percent of participants who have one of the following: a baseline HAI titer of  $<10$  and a post vaccination titer of  $\geq 40$ ; or a baseline HAI titer of  $\geq 10$  and a  $\geq 4$  fold increase post vaccination (6). Using HAI response as a correlate of protection, we will also be able to estimate the duration of protection and correlate immunologic outcomes with influenza-associated ARI and SARI among the elderly.

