#### **7.1.5 Number of participants**

Sample size for cohort: The cohort sample size is calculated assuming a 50% vaccination rate, 80% power, a probability of committing a type I error of 5% and an incidence of influenza-associated ARI of 6% per year. With an expected VE of 40% based on our population's age and past studies (12, 16, 17), the required sample size is 2,724. Given a 15% loss to follow-up, a total of 3,133 persons should be enrolled, and assuming a 10% refusal rate, a total of 3,446, or, for simplicity, 3,500 individuals need to be selected

These sample sizes were calculated in OpenEpi.com(47) using the Fleiss Method with a correction factor as follows:

Fleiss Method:

$$n_1 = \frac{[Z_{\alpha}\sqrt{(r+1)\bar{p}\bar{q}} + Z_{1-\beta}\sqrt{rp_1q_1 + p_2q_2}]^2}{r(p_1 - q_1)^2}$$

$$n_2 = rn_1$$

where  $n_1$  is the number of cases and  $n_2$  is the number of controls,  $\bar{p}$  is the average exposure in the population,  $\bar{q}$  is  $1-\bar{p}$ ,  $p_1$  is the proportion of cases with the exposure,  $q_1$  is  $1-p_1$ ,  $p_2$  is the proportion of controls with exposure and  $q_2$  is  $1-p_2$ .

To account for the use of a normal distribution to approximate a binary function, a continuity correction is applied to  $n_1$  as follows to calculate the final sample size,  $n_{cc}$ :

$$n_{1cc} = \frac{n_1}{4} \left[ 1 + \sqrt{1 + \frac{2(r+1)}{n_1 r |p_2 - p_1|}} \right]^2$$

$$n_{2cc} = rn_{1cc}$$

where  $n_{1cc}$  and  $n_{2cc}$  are the corrected sample sizes of  $n_1$  and  $n_2$ , respectively.

Sample size for changes in functional status related to ARI or SARI: We will select matched pairs and compare functional status (measured on a 10 point scale by the VES-13) three-four weeks after the onset of an influenza-associated ARI or SARI to a control who has not had an ARI or SARI. As functional status is measured on continuous scale of 1-10, a matched dependent  $t$  test is used to compute sample sizes. We have used the PROC POWER procedure in SAS

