**For secondary objective 2.2 (Immunogenicity)**

Elderly who have not yet been vaccinated, but have presented to the district hospital for vaccination will be asked by trained study staff at the district hospital to join the immunogenicity subset of the study regardless of whether they joined the primary study. Elderly will be informed of the objective aim, protocol, risks and benefits of joining the immunogenicity study. If elderly consent, they will be asked to have blood drawn before being vaccinated with the inactivated, trivalent influenza IIV3 vaccine the same day (day 0), and return to the district hospital again to have blood drawn 28 days (1 month), 180 days (6 months) and 360 days (1 year) after receiving the vaccine. One additional blood draw will be requested after 28 days of second vaccination in the year 2 to compare the effect of prior vaccination on level of immunological response. For participants unable to travel to the health center, the research nurse will travel to the elderly participant's home and obtain the necessary blood sample, and transport the sample back to the district hospital in ice packs. Participants will be asked for 5cc of blood per scheduled appointment. The serum will be separated from the blood samples using a centrifuge at the district hospital and stored in a refrigerator between 4-8°C for a week or less. On a weekly basis, the serum samples will be transported in ice-packs for less than 24 hours to the NIH laboratory in Nonthaburi. When participants consent to being enrolled, the study staff that consents and enrolls them will also take an electronic baseline assessment questionnaire CRF that should take about 15 minutes to administer. They will provide the participant with a study ID card which has their individual study number and the days of their next scheduled appointments. The card will also have a number to call a study team member if the participant should need to reschedule their appointment or has any other issues or concerns.

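### Section 7.9 reads vaccine antibody persistence from all late titres, including those raised by influenza infection, so persistence is biased upward, modestly on the protocol's own inputs

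*Protocol*

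**What the plan says.** Protocol 7.9 takes blood before vaccination, at 28 days, and then "180 days (6 months), and 360 days (12 months) later". A random effects model compares the later titres with baseline "to determine how long participants vaccinated with IIV3 retain an adequate number of HI antibodies". The same paragraph says the method can "control for confounders such as age and factors which make participants immuno-compromised". Section 3.1.4, under laboratory testing of blood samples, goes a step further: "Using HAI response as a correlate of protection, we will also be able to estimate the duration of protection".

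Three other places matter.

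- Section 7.1.5 sizes the cohort on "an incidence of influenza-associated ARI of 6% per year" and 40% vaccine effectiveness.
- Section 8.1 asks participants to give notice before taking the next season's vaccine, so that the last draw can come first.
- Section 7.5.1 recruits into the immunogenicity sub-study "regardless of whether they joined the primary study", and 7.2 agrees that the two studies need not overlap. Section 7.10, however, describes the 384 as part of the 3,500 cohort members.

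**The concern.** The quantity wanted is how long antibody from the vaccine lasts. A titre at day 180 or day 360 reflects vaccination plus any influenza infection since. Infection raises the titre to the infecting strain, so keeping such titres can only flatten the apparent decline. If people whose titres have waned are infected more often, some vaccine failures end up counted as persistence.

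No unvaccinated serology group is sampled that would show the background level of boosting. The protocol sees the problem for one source, re-vaccination, and closes it in 8.1. It does nothing comparable for infection. At stake are the persistence curve for objective 2.2 and the statement about duration of protection drawn from it.

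**Working it through.** **Inputs from the protocol.** Influenza ARI 6% per year, effectiveness 40%, sub-study size 384, precision of 5 points either way, expected seroconversion 30 to 50% (all 7.1.5); three strains measured separately (7.5.1).

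**Assumptions.** An infection raises the titre 4- to 8-fold, that is b = 2 or 3 on the log2 scale. The true share above an adequate titre at day 360, S, is 30 to 50%, borrowing the seroconversion range. Every infected person ends above the threshold. In these formulas infection does not depend on titre.

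**1. The stated size.** p(1−p) × 1.96² / d² = 0.25 × 3.8416 / 0.0025 = 384.16, so 384 reproduces for an infinite population. The printed finite-population formula with N = 15,000 gives 374.6. The precision of 5 points is a fair yardstick either way.

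**2. Which group the 6% describes.** Comparing 6.0% with 3.6% at 80% power with continuity correction gives 1,327 per arm, 2,654 in all, 2.6% below the stated 2,724. Taking 6% as the whole-cohort rate gives 7.5% (0.06 / 0.80) in the unvaccinated and only 2,098 in all. So 6% is the unvaccinated rate.

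**3. Infections among vaccinees.** 0.06 × (1 − 0.40) = 3.6% per year; 384 × 0.036 = 13.8, about 14 people. Split evenly over three strains (assumption) this is 1.2% per strain; 384 × 0.012 = 4.6, about 5 people.

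**4. Day-360 GMT.** Inflation = 2^(q × b), where q is the share infected before the draw.

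| q | 4-fold boost | 8-fold boost | A true 2-fold fall reads as |
|---|---|---|---|
| 1.2% (even split) | 1.017 | 1.025 | 1.97 to 1.95 |
| 3.6% (all one strain) | 1.05 | 1.08 | 1.90 to 1.86 |
| 10% (assumption) | 1.15 | 1.23 | 1.74 to 1.62 |

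**5. Day-360 proportion above threshold.** Observed share = S + (1 − S)q, so the shift is (1 − S)q.

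- q = 3.6%: 0.70 × 3.6 = 2.5 points at S = 30%; 0.50 × 3.6 = 1.8 points at S = 50%.
- q = 1.2%: 0.8 and 0.6 points.
- q = 10.8% (total infections three times the symptomatic ones, assumption): 7.6 and 5.4 points.

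These are year-end figures. Fewer infections have accrued by day 180.

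**The case against.** The strongest reply is that this is detail for a statistical analysis plan. The list of confounders in 7.9 is open, no sentence there is false, and 3.1.4 plans to "correlate immunologic outcomes with influenza-associated ARI and SARI among the elderly", so infection data are to be linked to titres. Part of this stands: an analysis plan not shown could add a censoring rule, and 7.9 does not rule one out. But the protocol fixes both the model and the interpretation, and correlating titres with illness does not remove boosted titres. Nor could a later plan create swab results for people who were never under surveillance.

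The reply on size is largely right. A reader might infer that a two-fold fall would read as about 1.6-fold. That needs 10% infected and an 8-fold boost, neither of which is in the protocol. HAI is measured per strain, while 3.6% covers all influenza. On the protocol's inputs the shift lies inside the design precision.

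A reader might also infer from 7.5.1 that many sub-study members go unswabbed. Section 7.10 implies that all are cohort members. The sections conflict, and the share outside the cohort cannot be known from the text.

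Finally, an exclusion rule has its own bias. If waners are infected more often, dropping them removes faster waners. A four-fold rise in any of three strains will also catch assay noise: simulations without infection (assumed assay SD 0.5 to 0.7 log2) flagged from a few percent to nearly a fifth of participants and lowered the day-360 GMT by up to about 5%. This argues for a rule applied strain by strain, with both results shown. It does not argue for having no rule.

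**Conclusion.** The point holds. As written, 7.9 estimates antibody from vaccine or infection and interprets it as vaccine persistence, and the bias is upward. On the protocol's inputs it is modest: 5 to 8% on the day-360 GMT in the least favourable case of one strain, about 2% per strain under an even split, and about 2 points on the proportion above threshold. Larger effects require that unswabbed or asymptomatic infection is common, which the documents neither state nor exclude.

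The documents do not support reading this as a defect that invalidates objective 2.2. The day-28 response is largely unaffected, and the influenza incidence comparison in objective 1.1 does not rest on these titres. It is worth correcting because the direction is known and the remedy is cheap.

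**What to change.** In 7.9, apply the following separately for each strain.

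- Flag an intercurrent infection when there is a PCR-positive swab attributable to that strain (cohort members), or a four-fold or greater rise in that strain's titre between consecutive post-vaccination draws (28 to 180, 180 to 360).
- Test the consecutive sera in the same assay run. The protocol ships serum weekly and does not mention paired testing, so this has to be settled before the assays are done.
- Exclude that strain's titres from the first affected draw onward in the vaccine-persistence estimate.
- Report the all-titre estimate beside it, worded as antibody from vaccine or infection, and limit the duration-of-protection statement in 3.1.4 to match.

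Reconcile 7.10 with 7.2 and 7.5.1 on whether sub-study members must belong to the cohort. For any who do not, only the serological flag is available.

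Cost: no extra blood and a few percent of late titres lost. Smaller rises stay undetected, some flags will be assay noise (a slight downward bias), and excluding infected people may remove faster waners. In simulations with assumed boost, assay noise and titre-dependent infection, a strain-specific or PCR-based rule cut GMT inflation from 1.07 to about 1.02 at 3.6% infected in one strain, and from 1.20 to about 1.06 at 10%. Bias is reduced, not removed, which is why both results should be reported.
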